### Intervention

The intervention will consist in the application of MI by the endocrinologist at four follow-up visits, held at 4-month intervals.

These visits proceed in the same way as standard appointments, with the addition of this new clinical approach. The visits last approximately 15–20 min, in accordance with routine hospital practices.

At each visit, the practitioner applies the four processes of MI (12):

Engaging. This first stage serves to establish a therapeutic relationship of trust and mutual respect, if this has not already been achieved.Focusing. This stage is a continuous process of searching for and maintaining direction. The aim is to place the emphasis on the “focus”, i.e., the aspect that the person wants to change. It is not a static process; it may be that in other stages it is necessary to change course and renegotiate the objectives.Evoking. This stage is aimed at eliciting “change talk” from the patient, so that he or she persuades him or herself to change. It begins with the expression of a desire, reason, or need. This stage promotes self-efficacy, one of the most powerful predictors of successful behavior. MI promotes change because it impacts on people’s self-efficacy.Planning. This stage is characterized by the presence of specific actions. There is less maintenance talk (regarding the behavior to be changed) and more change talk. The person begins to visualize the change and imagines the possible positive results. MI ends when the person commits to the plan.

Before the first appointment and 4 months after the fourth appointment, the participants complete the questionnaires. In each of the five visits the HbA1c value will be recorded.

A sample of 25 baseline appointments 1 was videotaped in order to assess the application of MI, and serve as ongoing training for the practitioners. A similar procedure will be followed for appointment 4. The practitioners who apply MI have previously received training.

#### Professional Training

MI is a set of skills designed to help patients overcome their ambivalence to change by evoking motivation and commitment. Professionals can gain expert experience in this method, for example, through an eight-step program (Motivational Interviewing Network of Trainers- MINT), which can be completed in 16 h.

The three endocrinologists have received structured MI training through theoretical-practical workshops taught by a psychologist with previous training and experience in MI. The workshops, which included didactic instruction and interactive exercises, were divided into two 3- to 4-h sessions and two to four additional 60- to 90-min encounters. The training started 3 months before recruitment, continued until the intervention began and addressed the contents established by MINT (**Table 1**). Interactive exercises included interviews conducted with real playing (i.e., colleagues who proposed something they would like to change, in order to make the practice more realistic), as well as role playing (i.e., using cases that are built on the context of T1D). Furthermore, real-patient interviews were overseen by the psychologist, both directly and through visualization of video recordings, and feedback was provided. Finally, all researchers read the MI book “Motivational interviewing: helping people change” (15). In addition, as a reminder, they were given a magnet on which the main tasks associated with MI are printed, to be put up in a visible place in their unit.

**Table 1 T1:** Contents of the theoretical-practical MI workshop.

*Spirit of MI*	Openness to a new model of thinking and doing with respect to patients. Developing active curiosity to understanding the patient’s perspectives, seeking to evoke the motivation for change in the patient him/herself. The spirit of the MI is based on four principles: collaboration, acceptance, evoking and compassion.
*Acquiring patient-centered counseling skills (OARS: open questions, affirmation, reflection, summary)*	Acquiring skills in the use of patient-centered communication. The key tools of MI are developed: empathy, open questions, affirmation, reflections for feedback, and summaries to take stock.
*Recognizing and reinforcing talk of change*	Developing the ability to recognize patients’ talk of change when it appears naturally in the context of ambivalence. Paying attention to expressions indicating desire, possibility, motives or need, and which predict the commitment to change.
*Eliciting and strengthening talk of change*	Helping professionals to strengthen talk of change once it has been recognized. The aim is to evoke talk of change deliberately instead of waiting for it to occur naturally.
*Rolling with resistance*	Learning to avoid resistance and responding to it appropriately if it appears. Practitioners should adjust to resistance rather than oppose it, through strategies of simple and complex reflections.
*Developing a change plan*	Developing the skill to attempt the transition from change talk to the development of an action plan to achieve it. The usual process is to offer a progressive summary of the change talk provided by the patient (desire, ability, motives and need) and then pose an open question whose essence is “What are you going to do now?”
*Consolidating patients’ commitment*	Once the plan is established, the crucial step is to maintain the patient’s commitment. The skills in this stage are the same as the ones developed in the other stages, since the fundamental thing is to listen to and support the patient’s language of commitment, understood as language that entails a decision once the action plan has been designed.
*Combining MI effectively with other tools*	MI is not the only tool in a professional’s repertoire. Patients who are prepared for the change should not be interviewed with MI, as it might be frustrating. It is part of the professionals’ task to recognize when to apply MI.

To avoid skill erosion and further improve MI performance, regular coaching and feedback-based, post-training sessions were held at baseline and are repeated at 2- to 3-month intervals during the intervention trial, to adhere to evidence-based practices (31). Individual reading of the book “Motivational Interviewing in Diabetes: facilitating self-care” (32) will complement the post-training sessions.

### Control Group

Patients randomly assigned to the control group will receive their four follow-up visits with standard medical care. The visits will be held with the same health practitioners, at the same intervals as in the intervention group, and will last a similar length of time. At each of the visits the HbA1c will be recorded, and before the first visit and 4 months after the fourth visit controls will complete the questionnaires in the same way as the intervention group.

### Interventions: Concomitant Care

Participants will continue with their usual follow-up routine for diabetes care. They are not asked for anything additional.

### Patient and Public Involvement

The results of the study will be presented to the scientific community at scientific meetings and in a research article. The results will also be disseminated in the local press and on the web page of the research group. Patients will also be informed of the results at the diabetes unit, once the trial has finished.

### Measures

The main variable of the study is adherence to self-care, measured through a validated questionnaire, the Diabetes Self-Care Inventory-Revised version (SCI-R). The secondary variables are: HbA1c, self-efficacy (EAG), health-related Quality of Life (ViDa1), satisfaction with the doctor-patient relationship, motivation for self-care, satisfaction with self-care, degree of fulfilment of a personal goal initially proposed by the participant, and a series of sociodemographic and clinical variables listed below. The time intervals for the measurements are shown in **Table 2**.

**Table 2 T2:** Time points of measurements.

Variable	Appointment 1 baseline	Appointment 2 4m	Appointment 3 8m	Appointment 4 12m	Appointment 5 16m Post-intervention
Primary outcome measure					
Adherence to self-care (SCI-R)	X				X
Secondary outcome measures					
*HbA1c*	X	X	X	X	X
Self-efficacy (GSE)	X				X
Health-related quality of life (ViDa1)	X				X
Motivation for self-care	X				X
Satisfaction with self-care	X				X
Satisfaction with the doctor-patient relationship					X
Personal goal of diabetes care	X				X
Sociodemographic data	X				X
Clinical data	X				X

#### Adherence to Self-Care Behaviors

The validated Spanish version of the SCI-R (33) will be used. This inventory consists of 15 items referring to self-care behaviors in the treatment of diabetes, which are scored on a Likert scale ranging from (1 = “never” to 5 = “always”). The scores are converted with a formula, and the responses range from 0 to 100; higher scores indicate higher levels of self-care.

#### Structured Self-Administered Data Collection Sheet

This data sheet is designed specifically for the study and it covers the following sociodemographic and clinical variables: sex, age, level of education (unschooled, primary, secondary, and university studies), employment status, living arrangements, duration of disease, type of drug treatment, treatment with psychoactive drugs, carbohydrate count, level of training in diabetes, diabetes chronic complications, and the limitation they represented for participants’ daily lives, number of hypoglycemia episodes per week, number of daily capillary glucose readings, and previous history of acute complications (admissions for severe hyperglycemia or hypoglycemia). Medical variables are confirmed *via* the patients’ medical history.

#### HbA1c

Glycated hemoglobin (HbA1c) (measured by HPLC or by point-of-care Alere Afinion AS100, standardized against DCCT/NGSP) is the standard measure for evaluating glycemic control over the last 2–3 months. The ADA recommendations suggest a general target level for HbA1c of less than 7% to reduce risk of diabetic complications (11).

#### Self-Efficacy

The General Self-Efficacy Scale (34) is administered in its validated Spanish version (35). This scale measures respondents’ expectations regarding their ability to cope adequately with a problematic situation. Responses are recorded on a Likert scale (1 = “not at all” to 5 = “totally”) and the score range is 1–50. Higher scores indicate a higher perception of self-efficacy.

#### Health-Related Quality of Life

Health-related quality of life is measured with the ViDa1 (36), which contains 34 items grouped in four dimensions: interference of diabetes in daily life, self-care, well-being, and worry about the disease. The response format is a Likert scale ranging from (1 = “strongly disagree” to 5 = “strongly agree”). A total score is obtained for each subscale, with a higher value indicating a higher level of the respective aspect.

#### Motivation for Self-Care

Motivation for self-care is measured on a Likert scale of 1–10, where 10 is the maximum score. This item is formulated specifically for this study.

#### Satisfaction With Self-Care

Satisfaction with self-care is measured with a Likert scale of 1–10, where 10 is the maximum score. This item is formulated specifically for this study.

#### Doctor-Patient Relationship Satisfaction

Satisfaction with the doctor-patient relationship is measured with a Likert scale of 1–10, where 10 is the maximum score. This item is formulated specifically for this study.

#### Personal Goal

Patients set themselves a health-related goal which they aim to achieve through their participation in the trial. The degree of achievement is measured with a Likert scale (1–10).

#### Intervention Fidelity Assessment

To evaluate the application of MI by the practitioners, video recordings of 25 patients were carried out at the first visit. At the fourth visit, all patient interviews will be recorded, and a random sample of 25 will be evaluated. A mobile phone with a tripod and an external memory card are used to make the video recordings. The recordings will be evaluated by two external observers using the Motivational Interviewing Rating Scale (MIAS/EVEM 2.0) (37). This scale has been previously validated for the application of MI in primary care; applied to several clinical sessions, it discriminates between the sessions in which the method has been used (and establishes to what degree) and the ones in which it has not been used. The raters will not know *a priori* to which group the patients in the recordings have been assigned.

### Analysis

Based on the number of patients followed in the clinic and the percentage with an HbA1c above 8%, we estimated that each of the three clinical researchers involved in the trial would be able to recruit around 20 patients in 4 months. With an expected sample size of 60 participants, we would be able to detect inter-group differences of 12.8 points on the SCI-R questionnaire and of 0.85% in HbA1c, with a power of 90% and a two-sided alpha of.05 [assuming an SD of 15 points in the SCI -R and 1% in HbA1c in line with previous studies (5)]. The equivalent detectable differences with a power of 0.8 would be 11 points and 0.74% respectively (calculated with http://hedwig.mgh.harvard.edu/sample_size/js/js_parallel_quant.html). This was an approximate estimation assuming the normality of the variable.

In order to retain most of the patients during follow-up, if someone misses an appointment, the patient is contacted and the visit is re-scheduled. Specific efforts will be made for the final evaluation visit. If a physical appointment cannot be achieved, the questionnaires will be sent and completed by e-mail or, if this is not feasible, the patient with be interviewed by phone. We expect the loss to follow-up to be below 10%.

Intention to treat analysis will be performed: i.e., all randomized participants who have attended at least one intervention (or control) session will be included in the analyses. The main analysis for primary and secondary outcomes, except HbA1c, will be a generalized linear model (GLM) including the intervention arm, the baseline score of the dependent variable and other variables imbalanced at baseline as covariates. The dependent variable will be the post-intervention score. The GLM does not need a normal distribution in the dependent variable (38), although the distribution of the variables will be analyzed using de Shapiro- Wilk test to perform an adequate descriptive analysis. The choice of the link function will depend on the distribution of the variable.

For the HbA1c, a GLM for multilevel analysis will be used including the intervention arm, baseline HbA1c and other imbalanced variables in the baseline as covariates. First-level are those corresponding to each measurement along follow-up (repeated time measurements); the second level includes patients’ variables. The model will also include an interaction term between the intervention-arm and time (follow-up), allowing for differences in the intervention effect between follow-up assessments (39). The effect that identifies the intervention arm is considered fixed, whereas the intercept is considered random. An autoregressive [AR (1)] covariance structure will be used in the model.

Other variables will be added as confounders in the model, as secondary sensitivity analyses. We will first fit separate models including each confounder, one at a time. Those variables whose inclusion in the model changes the estimates’ treatment effect by at least 10% will be considered as confounders. As suggested in the CONSORT statement, decisions about confounders will not be based on P value  (40).

In the case of missing values, these will be accommodated with multiple imputation procedure in Stata 15.0 software (Stata Corporation) (41). This procedure saves cases for the analysis and can be considered an intention-to-treat analysis. Analysis under multiple imputations is valid for randomly missed data (42). A threshold of.05 will be used to define the statistical significance of those tests.

For the MIAS/EVEM 2.0 scale, the Intraclass Correlation Coefficient (ICC) will be used.

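### The main models pick covariates by observed baseline imbalance rather than by prognosis, at a modest cost in power, and the 10% change-in-estimate rule for the sensitivity analyses selects uninformatively when the effect is small

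*Protocol article*

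**What the plan says.** All of this stands in the Analysis section of the protocol article.

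- **Primary outcome and all secondary outcomes except HbA1c:** a generalized linear model for the post-intervention score, with arm, baseline score and "other variables imbalanced at baseline as covariates".
- **HbA1c:** a multilevel model with arm, "baseline HbA1c and other imbalanced variables in the baseline as covariates", and an arm-by-time interaction.
- **Sensitivity analyses:** "Other variables will be added as confounders in the model, as secondary sensitivity analyses". Variables are entered one at a time, and the selection rule is: "Those variables whose inclusion in the model changes the estimates’ treatment effect by at least 10% will be considered as confounders". The section adds that "decisions about confounders will not be based on P value".

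No covariate beyond the baseline value of the outcome is named, and the article attaches no criterion to imbalance. Practitioner, by which the randomization is stratified (Randomization and Blinding), is not among the covariates. The Discussion says that there are too few professionals for their effect to be included in the analysis.

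**The concern.** Covariate adjustment in a randomized trial gains precision when the covariate predicts the outcome. A difference between arms at baseline carries no information about that. A rule based on imbalance therefore spends degrees of freedom on variables that may be irrelevant, and it passes over a strong predictor that happens to be balanced. It also leaves the composition of the primary model unknown until the baseline table by arm has been seen.

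The 10% rule has a different defect. Its threshold is a fraction of the estimated treatment effect, so the bar almost vanishes when the estimate is near zero and is high when the estimate is large. Which variables count as confounders then depends mainly on the size of the estimate and little on the variables themselves.

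At stake are some power in a trial of 66 patients, whose Discussion concedes that it may miss smaller but relevant effects, and the usefulness of the sensitivity analyses.

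**Working it through.** **Inputs from the protocol article.** Expected sample 60 (30 per arm), SD 15 points on the SCI-R, two-sided alpha 0.05, detectable differences 12.8 points (90% power) and 11 points (80%); 66 patients included. The self-administered data sheet lists about 15 sociodemographic and clinical variables. Table 2 adds baseline HbA1c, self-efficacy, quality of life, motivation, satisfaction with self-care and personal goal, so about 20 candidates is a fair count.

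**Assumptions not in the article.** Correlation of 0.5 between baseline and final score; 20 independent candidates, of which three are prognostic (r = 0.35, 0.2, 0.2); individual allocation in equal arms.

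**1. The plan's own figures.**
- 90% power: (1.960 + 1.282) × 15 × √(2/30) = 12.55 points; 12.77 with the t distribution on 58 df. Stated: 12.8.
- 80% power: (1.960 + 0.842) × 15 × √(2/30) = 10.85; 11.03 with t. Stated: 11.

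Both reproduce.

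**2. How many variables enter.** The chance that one variable shows a standardized difference above 0.2 is 2[1 − Φ(0.2/√(2/n))].
- n = 30 per arm: 2[1 − Φ(0.775)] = 0.439.
- n = 33 per arm: 2[1 − Φ(0.812)] = 0.417.

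Of 20 candidates, 20 × 0.439 ≈ 8.8 would enter on that reading. If imbalance means p < 0.05, 20 × 0.05 = 1 would enter.

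**3. Power at 11 points** (ANCOVA, 3,000 simulated trials):

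| Covariates besides arm and baseline score | Power |
|---|---|
| imbalanced at p < 0.05 | 86.8% |
| imbalanced at p < 0.10 | 85.5% |
| standardized difference > 0.2 | 84.0% |
| standardized difference > 0.1 | 83.7% |
| none | 88.9% |
| one pre-named covariate, r = 0.35 | 92.8% |

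The rule costs 88.9 − 86.8 = 2.1 to 88.9 − 83.7 = 5.2 percentage points against the baseline score alone. Repeat runs agree to within about one point.

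**4. Type I error.** Each imbalance criterion, applied alone, rejects in 3.5 to 5.1% of null trials across runs. Taking the smallest p-value over the four imbalance readings gives 8.1 to 8.3%. Adding the model with no extra covariate as a fifth option gives 9.0 to 9.6%. A separate set-up with 15 candidates and five imbalance criteria gives about 8%.

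**5. The 10% rule, for a covariate unrelated to the outcome.** Adding it shifts the estimate by about (its fitted slope) × (its baseline difference).
- Residual SD after the baseline score: 15 × √(1 − 0.25) = 12.99.
- SE of the slope per SD of covariate: 12.99/√60 = 1.68.
- SD of the baseline difference: √(2/30) = 0.258.
- Scale of the shift: 1.68 × 0.258 = 0.43 points. Its mean absolute size is (2/π) × 0.43 = 0.28, and its median is about 0.16.
- SE of the treatment estimate: 12.99 × 0.258 = 3.35. With no true effect the median absolute estimate is 0.6745 × 3.35 = 2.26, so the bar is typically only 0.23 points. At a 12.8-point estimate it is 1.28.

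A shift of this size often clears 0.23 and seldom clears 1.28. Simulated flagging rates agree: 42 to 45% at zero effect, 24 to 25% at 5 points, 3 to 4% at 12.8 points.

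**The case against.** The best defence has five parts.

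- **Type I error.** Selection on baseline data and arm does not by itself inflate the error rate. This stands. A reader might infer that the primary test runs at 9% or more. The article does not support that: the figure needs someone to fit several versions and keep the best, and a threshold is something an analysis plan may fix.
- **Blinding.** Randomization and Blinding says that those who analyze the data will not know the allocation. That limits steering towards one arm. It does not prevent a choice among models by p-value under coded arms, and it does not recover power.
- **Imbalance may not be pure chance.** The arm of the first participant of the day applies to everyone seen that day, so imbalance could be clustered, and some adjustment has a rationale. This stands, but it does not make imbalance a good criterion for choosing covariates.
- **The 10% rule is secondary.** It cannot change the main estimate, and a falsely flagged variable usually moves the estimate by a fraction of a point on a 0 to 100 scale. A reader might infer that the sensitivity analyses are misleading; the supported statement is that their selection step is uninformative. Nor can one say in general that a non-identity link triggers the rule without confounding: mean ratios under a log link are collapsible.
- **The strongest predictor may already be in.** The baseline score is always in the model, so the rule cannot drop it. The gain to 93% depends on being able to name a further covariate with r of about 0.35, a value no passage supplies. Every variant also exceeds the 80% power planned at 11 points.

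**Conclusion.** The point holds in moderate form. Both rules are stated in the article and are poor as stated; this is not merely detail left to an analysis plan, because a threshold would not turn imbalance into a guide to prognosis.

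Under the assumed correlations, the main-model rule does worse than adjusting for the baseline score alone by about 2 to 5 percentage points of power at 11 points. It falls further behind a model with a well-chosen named covariate. The primary test remains valid under any single fixed criterion; the risk of 8 to 10% arises only from choosing among readings.

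The 10% rule selects noise often when the effect is small and rarely at the design effect, with little numerical consequence either way. The simulated sizes rest on independent candidates and individual allocation. The direction of both findings follows from the rules themselves.

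**What to change.** - Before unblinding, name the covariates of the main model: the baseline score of the outcome plus one or two variables expected to be prognostic. Baseline motivation for self-care is a documented candidate: the Background reports it as the leading predictor of adherence in a previous study, and Table 2 schedules it at baseline.
- Add practitioner, the stratification factor, as a fixed effect. Three practitioners need two parameters. Reconcile this with the Discussion: too few professionals to estimate a variance component is not a bar to a fixed effect.
- Delete "other variables imbalanced at baseline as covariates" from the main model and "other imbalanced variables in the baseline as covariates" from the HbA1c model.
- Replace the 10% rule with one pre-named extended covariate model as the sensitivity analysis, reported whatever it shows.

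The cost is a change of protocol wording, with the matching text in any analysis plan; no new data are needed. The downside is that a striking imbalance, by chance or through the day-level assignment, is then handled only in the sensitivity analysis.
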